
#### Neuropsychological Test

To confirm that the children who wished to participate in the study meet the research criteria, the K-WISC-IV test, an intelligence test that comprehensively evaluates the overall intellectual ability of children, will be performed before the start of the study [27]. To compare and evaluate the effectiveness of the metaverse-based social skills training program developed in this study, a series of neuropsychological tests will be performed before and after the study to evaluate sociability. Neuropsychological tests to be used in the study include the Social Responsiveness Scale (SRS), evaluated by parents, as a tool to verify the effectiveness of children's social interactions. Furthermore, the Korean version of the Child Behavior Checklist (K-CBCL) and the Korean version of the Vineland Adaptive Behavior Scale-2 (K-VABS-2) test are used as evaluation tools to verify the children's overall problematic behavior, adaptability, and sociability-related effects as determined through a parental survey. The Children’s Depression Inventory (CDI) and revised Children’s Manifest Anxiety Scale (RCMAS) are used as assessment tools to compare mental health levels, such as stress relief, depression, and anxiety before and after intervention.

#### Biometric Information

During the 4 weeks of this study, all children participating in the study will use a wearable device shaped like a smartwatch (Fitbit) to minimize discomfort. In addition to collecting the children's biometric information using the smartwatch, a webcam will be used to record the children's behavior and facial expressions in real time during the program. The biometric information of the children with ASD will be compared and analyzed using the internet-based (metaverse) program with the biometric information of children with ASD and real-time biometric information recorded daily. Based on the study results, the effectiveness of the metaverse-based social skills training program using digital technology will be verified, and the children's anxiety and stress levels will be measured. The improvement of social interaction abilities has an important effect on children's adaptation to school life; therefore, its effect on improving mental health while alleviating stress and anxiety will also be verified.

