**Methods:**

This parallel randomized controlled study will be conducted on children aged 7-12 years diagnosed with ASD. A metaverse-based social skills training program using digital technology will be administered to children who voluntarily wish to participate in the research with consent from their legal guardians. The treatment group will participate in the metaverse-based social skills training program developed by this research team once a week for 60 minutes per session for 4 weeks. The control group will not intervene during the experiment. The treatment group will use wearable devices during the experiment to collect real-time biometric information.

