## Methods

### Study Design

#### Summary

This study is a parallel randomized controlled study (trial registration: KCT0006859) involving children aged 7-12 years diagnosed with ASD who volunteered to participate in the study with the consent of a legal guardian. The study will include an intervention group and a control group at a 1:1 ratio. Participants will be publicly recruited through the internet to enroll in a clinical trial through the Korean-Wechsler Intelligence Scale for Children-IV (K-WISC-IV) test administered by a professional clinical psychologist. Following neuropsychological evaluation, the children eligible for this study will be assigned randomly to the intervention or the control group for 4 weeks. Randomization will be performed using the PROC PLAN method in the SAS software program (version 9.4, SAS Institute). In this study, we plan to develop and apply a social skills training program for children with high-function ASD that can be implemented within the metaverse platform based on the PEERS program using digital technology. The PEERS is a social skills training program developed for children with ASD who face difficulties in making or retaining friends. The PEERS program has 14 sessions. The 1st session gives the introduction and trading information; the 2nd session is about conversational skills; the 3rd session is on electronic communication; the 4th session is about choosing appropriate friends; the 5th session is regarding the appropriate use of humor; the 6th session is about peer entry strategies; the 7th session is regarding peer exit strategies; the 8th session is about get togethers, the 9th is on good sportsmanship; the 10th is about handling teasing; the 11th is on handling bullying and bad reputations; the 12th is regarding arguments and disagreements; the 13th is about handling rumors and gossip; and the 14th one includes a graduation party and ceremony [12]. Under the guidance of a clinical psychologist (with a PhD in education) and a clinical specialist in psychiatry, “Becoming a Good Sportsman,” which is part of the PEERS program, was selected and conducted as a proof-of-concept study. Socializing with peers is important for children and adolescents with ASD to build close friendships and engage in positive peer interactions. To reduce the burden of discussing a wide range of topics, it is better to proceed with activities that go well together. “Becoming a Good Sportsman” was selected because experts considered it suitable for a test study because it is composed of activity-based socializing to become a good sportsman, which corresponds to the ninth session selected in our study [26]. To maintain the consistency of the program, a professional clinical psychologist trained during the study period will conduct it. To verify the effectiveness of the program, the results of neuropsychological evaluation, including social development indicators and biometric information (heart rate, heart rate variability, saturation, respiratory rate, and stress index), will be collected through wearable devices. Children enrolled in the study will be randomized into 2 groups with the same baseline characteristics. To verify the effectiveness of the program, for each group, first the differences between the neuropsychological evaluation results, including the social development index determined before the experiment and the test results after the experiment, will be compared and analyzed using a statistical method. Second, the differences in the neurophysiological scores between the groups will be compared and analyzed. Based on the results of these 2 processes, the effectiveness of the metaverse-based social skills training program using digital technology will be verified.

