#### Intervention Group Receiving the Metaverse-Based Social Skills Training Program

The intervention group will receive the metaverse-based social skills training program developed by the researchers for 60 minutes per session once a week for 4 weeks. The program consists of direct instruction (rules for being a good sportsman) and practical training (playing sport games). Table 1 summarizes the metaverse-based social skills training program content. When the program is applied to metaverse, a wearable device will collect the child's biometric information in real time. In addition to internet-based and offline recording modes, the children's actions will be recorded using a webcam during the program.

**Table 1 table1:** Contents of the metaverse-based social skills training program.

Week	Session	Goal	Content
1	Introduction and preneuropsychological test (offline)	Orient the participants to the program	Explaining the process involved in the program and the basic rules and the use of the wearable device Preneuropsychological evaluation
2	Being a Good Sportsman 1(internet): awareness of the need for rules and results	Learn and develop the right behavior for replacing inappropriate behavior; avoid uncontrolled negative behavior to achieve positive behavior	Subject and modulator introducing themselves to each other Self-introduction by team Forming rules Playing sports games in metaverse Giving session feedback and homework
3	Being a Good Sportsman 2 (internet): understanding the situation and participating in team activities	Learn social understanding by noticing situations and conflicts that occur during team activities	Greeting therapists and participants Checking the homework from the last session Reminding rules Playing sports games in metaverse Giving session feedback and homework
4	Being a Good Sportsman 3 (internet): responding appropriately to negative behavior experiences and negative emotions	Learn to accept the result of rule violations, failures, etc experienced in team activities and understand appropriate emotional response	Greeting therapists and participants Checking the homework from the last session Educating and practicing negative emotion acceptance and coping skills Playing sports games in metaverse Giving session feedback and homework

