### Control Group

The control group will not intervene. Only neuropsychological tests will be conducted between the first and last week.

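### The article contradicts itself on which arms wear the device, so the biometric part of the effectiveness claim may have no control data

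*Protocol article*

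**What the plan says.** The protocol article describes device wear in several places.

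- **Biometric Information:** for the 4 weeks of the study, "all children participating in the study will use a wearable device shaped like a smartwatch (Fitbit".
- **Abstract, Methods:** "The treatment group will use wearable devices during the experiment to collect real-time biometric information". The sentence just before it, on the control group, mentions no device.
- **Control Group:** "Only neuropsychological tests will be conducted between the first and last week".
- **Intervention Group section:** "When the program is applied to metaverse, a wearable device will collect the child's biometric information in real time". Table 1 places the explanation of the device in the program's introductory week, and the Discussion (Significance of the Study) again describes the device as used while the program is being run.

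It also gives the biometric data a role as evidence. In the Study Design summary, a sentence whose stated purpose is to verify effectiveness says that neuropsychological results and "biometric information (heart rate, heart rate variability, saturation, respiratory rate, and stress index), will be collected through wearable devices". The Biometric Information section compares recordings made during the program "with the biometric information of children with ASD and real-time biometric information recorded daily", and goes on to say that the results will verify the program's effectiveness. The summary's analysis outline ends with this step: "Second, the differences in the neurophysiological scores between the groups will be compared and analyzed".

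**The concern.** Which children wear the device is a decision about data collection. No later analysis can recover control recordings that were never made. The two versions of the text also support different conclusions. With recordings in both arms, a randomized biometric comparison is possible. With recordings in the treatment arm alone, biometrics can describe how treated children respond but give no randomized evidence that the program works. The article claims biometric evidence of effectiveness without settling which version applies.

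**Working it through.** The article states no statistical figure on this point, so the check is a comparison of the text and a count of children.

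**Inputs.** Total recruited: 24 (Screening and Inclusion Criteria). Allocation: 1:1 (Study Design summary). Per group: 12 (Sample Size). These agree: 2 × 12 = 24. Biometric measures named: 5 (heart rate, heart rate variability, saturation, respiratory rate, stress index). Program: one 60-minute session a week for 4 weeks.

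**Step 1: can the statements be reconciled?** The Abstract and the intervention section say that treated children wear the device. Neither says that controls do not, so each alone is compatible with wear in both arms. The Control Group section is different: it restricts what controls undergo to neuropsychological testing. On its natural reading that excludes 4 weeks of device wear, which the Biometric Information section requires of every child. These two sections conflict.

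**Step 2: data available under each version.**

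| Version | Treated children with biometric data | Control children with biometric data | Between-group biometric contrast |
|---|---|---|---|
| All children wear the device | 12 | 12 | Can be estimated |
| Treatment arm only | 12 | 0 | Cannot be estimated, for any of the 5 measures |

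**Step 3: what remains under the treatment-only version.** The available contrast is session recordings against daily recordings in the same treated children. Session time is at most 4 × 60 = 240 minutes per child. During it the child is playing sports games on the platform and receiving the program at once. The article describes no period of similar gaming without the program. A difference in heart rate or stress index could therefore come from the gaming, from the program, or from both.

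**Step 4: which parts of the plan depend on this.** The neuropsychological tests are given to both arms, so their between-group comparison is intact under either version. The third objective in the Introduction concerns emotional change in stressful situations. That is a question about change within children and needs no control arm. What is exposed is the use of biometrics to verify effectiveness, in the Study Design summary and the Biometric Information section.

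**The case against.** The strongest reply is that this is a slip of wording with little consequence. Its parts differ in strength.

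- **The between-group step is probably not biometric.** A reader might infer from "the differences in the neurophysiological scores between the groups will be compared and analyzed" that the trial's planned between-group comparison could lack control data. The documents do not support that. The sentence is the second of two steps, and the first concerns neuropsychological results before and after in each group. The Statistical Analysis section has the same structure, and no biometric score at baseline or posttest is defined anywhere. *Neurophysiological* is plausibly a slip for *neuropsychological*, and those scores exist in both arms. This part of the reply stands, and the word should be clarified.
- **The third objective is sound without controls.** A reader might count its within-child design as a defect, but that contrast is what the objective asks for. This also stands.
- **The Abstract does not restrict the device to the treatment group.** Correct. The exclusion rests on the Control Group section. One could argue that this section speaks of tests and not of monitoring, but that is a strained reading, and the article gives controls no other procedure.
- **Time of day can be handled.** Daily recordings over 4 weeks could supply the same clock hours on days without a session. This stands, so time of day is not an unavoidable confounder. Active gaming remains one.
- **This is a pilot, and its limits are acknowledged.** The Limitations section says that the effect cannot be generalized because of the small number of participants. That does not address a missing control arm for one class of data.

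None of this removes the conflict between the Biometric Information and Control Group sections, or the use of biometrics as evidence of effectiveness.

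**Conclusion.** The article is wrong as written on which arms wear the device. The consequence is conditional. If only the treatment arm wears it, 0 of 12 controls have biometric data on any of the five measures, and the biometric part of the effectiveness claim is an uncontrolled within-child contrast that cannot separate the program from active gaming. If all 24 children wear it, a 12 versus 12 comparison is available. The counts assume full recruitment at 1:1 and no lost recordings.

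The documents do not show which version is intended. More passages link the device to the program than assign it to everyone, so the all-children version should not be presumed. The point limits what may be concluded from the biometric data and leaves the neuropsychological comparison untouched.

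**What to change.** Reconcile the Abstract, the Biometric Information section, the intervention section and the Control Group section so that all say the same thing about which arms wear the device. Clarify whether *neurophysiological scores* in the Study Design summary means the neuropsychological scores. Then follow the version chosen.

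- **If both arms wear the device:** base any biometric statement about effectiveness on a treatment versus control comparison of recordings made outside session hours. Label session versus daily contrasts as within-arm and descriptive. Cost: up to 12 more devices for 4 weeks if only the treatment arm was equipped, and possibly an update to consent or ethics approval.
- **If only the treatment arm wears it:** remove biometrics from the verification of effectiveness in the Study Design summary and the Biometric Information section, and report them descriptively for the third objective. Cost: wording only.

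Either option resolves the point.

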#### Intervention Group Receiving the Metaverse-Based Social Skills Training Program

The intervention group will receive the metaverse-based social skills training program developed by the researchers for 60 minutes per session once a week for 4 weeks. The program consists of direct instruction (rules for being a good sportsman) and practical training (playing sport games). Table 1 summarizes the metaverse-based social skills training program content. When the program is applied to metaverse, a wearable device will collect the child's biometric information in real time. In addition to internet-based and offline recording modes, the children's actions will be recorded using a webcam during the program.

**Table 1 table1:** Contents of the metaverse-based social skills training program.

Week	Session	Goal	Content
1	Introduction and preneuropsychological test (offline)	Orient the participants to the program	Explaining the process involved in the program and the basic rules and the use of the wearable device Preneuropsychological evaluation
2	Being a Good Sportsman 1(internet): awareness of the need for rules and results	Learn and develop the right behavior for replacing inappropriate behavior; avoid uncontrolled negative behavior to achieve positive behavior	Subject and modulator introducing themselves to each other Self-introduction by team Forming rules Playing sports games in metaverse Giving session feedback and homework
3	Being a Good Sportsman 2 (internet): understanding the situation and participating in team activities	Learn social understanding by noticing situations and conflicts that occur during team activities	Greeting therapists and participants Checking the homework from the last session Reminding rules Playing sports games in metaverse Giving session feedback and homework
4	Being a Good Sportsman 3 (internet): responding appropriately to negative behavior experiences and negative emotions	Learn to accept the result of rule violations, failures, etc experienced in team activities and understand appropriate emotional response	Greeting therapists and participants Checking the homework from the last session Educating and practicing negative emotion acceptance and coping skills Playing sports games in metaverse Giving session feedback and homework
5	Being a Good Sportsman 4 (internet): knowing and accepting individual differences	To be able to recognize the characteristics of other team members and accept similarities and differences with friends while working as a team	Greeting therapists and participants Checking the homework from the last session Educating and practicing “knowing and accepting” skills. Playing sports games in metaverse Giving session feedback
6	Neuropsychological test (offline)	Conducting postneuropsychological evaluation	Postneuropsychologital evaluation: K-SCQ^a^ SRS 2^b^ K-CBCL^c^ K-VABS-2^d^ SCL-R^e^ CDI^f^ RCMAS^g^

^a^K-SCQ: Korean Version of the Social Communication Questionnaire.

^b^SRS-2: Social Responsiveness Scale-2

^c^K-CBCL: Korean version of the Child Behavior Checklist.

^d^K-VABS-2: Korean version of the Vineland Adaptive Behavior Scale-2.

^e^SCL-R: Symptom Checklist-Revision.

^f^CDI: Children’s Depression Inventory.

^g^RCMAS: revised Children’s Manifest Anxiety Scale

### Control Group

The control group will not intervene. Only neuropsychological tests will be conducted between the first and last week.

### Measures

#### K-WISC-IV Test

The K-WISC-IV is used to establish a baseline for the participating children. This test evaluates the overall cognitive function of children using 15 subtests, such as common sense, missing places, and vocabulary. The K-WISC-IV is an individual test tool used to evaluate the cognitive abilities of children aged 6-16 years [27]. The evaluation items include the verbal comprehension index (VCI), visual spatial index (VSI), fluid reasoning index (FRI), working memory index (WMI), and processing speed index (PSI) that are combined to evaluate intellectual ability. The VCI is a measure of crystallized intelligence. It measures a child’s ability to access and apply acquired word knowledge. The VSI measures a child’s ability to evaluate visual details and understand visual spatial relationships to construct geometric designs from a model. The FRI measures a child’s ability to detect the underlying conceptual relationship among visual objects and use reasoning to identify and apply rules. The WMI measures a child’s ability to register, maintain, and manipulate visual and auditory information in conscious awareness. The PSI measures a child’s speed and accuracy of visual identification, decision-making, and decision implementation. It provides composite scores representing the overall intelligence quotient (IQ) as well as subtests and composite scores representing intellectual functioning in specific cognitive domains [28].

#### Korean Version of the Social Communication Questionnaire (K-SCQ)

The SCQ is a tool that clinicians use when screening individuals for ASD. The parent or primary caregiver of the target child can easily answer “yes/no” and screen a wide range of symptoms related to autism in a short time. It was designed as a questionnaire version of Autism Diagnostic Interview-Revised (ADI-R) [29]. It is a screening tool consisting of 40 items asking parents or caregivers about their children's ASD-related symptoms (communication, reciprocal interactions, and restrictive and repetitive behaviors and interests). There are 2 forms, namely the Lifetime AutoScore Form and the Current AutoScore Form. The Lifetime Form provides an answer based on the individual’s overall development, and the Current Form provides answers based on the individual's behavior in the last 3 months. The K-SCQ was translated into English and approved by the authors [30].

#### Social Responsiveness Scale-2 (SRS-2)

The SRS-2 is an evaluation tool used to verify the effectiveness of social interactions. This test is a questionnaire that asks parents or teachers to evaluate the characteristics of social interactions that children have displayed in the past 6 months and consists of 65 items. Each question is rated from “not at all” (0 points) to “almost always” (3 points) and can be scored on a scale of 0-195 points. The evaluation content consists of social insight, social information processing, mutual social communication ability, social anxiety/avoidance, and autistic immersion and traits. Higher scores indicate lower social functioning [31].

